## Introduction

Prostate cancer (PCa) is the most common cancer in Finnish men and a major public health burden causing annually around 900 cancer deaths in Finland and the yearly costs caused by the disease are estimated to reach 180 million euros.^1 2^ However, not all prostatic malignancies are lethal; only 10%–20% of tumours advance to metastases and eventually into a fatal stage. Advanced PCa is treated by androgen deprivation therapy (ADT). Eventually, however, PCa progress despite the ADT treatment and forms state called castration resistance. Thus, castration resistance is clinically defined as a moment when PCa no longer responds to ADT treatment. Median time to castration resistance is 12–15 months and 45 months to death in patients who have started ADT for metastatic PCa.^3–7^ In men who start ADT for disease recurrence after primary treatment, median failure-free survival time is 33 months and 70 months to death.^3^

Blood cholesterol is likely a risk factor for PCa prognosis; risk of disease recurrence after primary treatment is significantly elevated in men with hypercholesterolaemia.^8^ Laboratory studies have demonstrated the importance of cholesterol for PCa cell growth.^9 10^ Furthermore, upregulation of intracellular lipid production and ensuing lipid accumulation is essential in surviving hypoxic tumour microenvironment.^11^ In PCa cells, it also assists in evading host-tumour immune response.^12^ Also, upregulation of intracellular cholesterol production appears to be central for development of castration resistance.^13^

Lipid metabolism is emerging as a new risk factor for PCa progression. The role of cholesterol is important in development of castration resistance, and inhibition of intracellular lipid production interferes with androgen receptor (AR) signalling essential for PCa progression.^13–15^ Cholesterol is precursor for intracellular androgen production, a central mechanism for PCa cells to overcome ADT.^13 15^ A recent study suggests that some of the serum basic lipid parameters may have increased association with development of castration resistance and metastasis especially in statin-naïve patients.^16^ Clarification of the role of lipid metabolism during ADT will likely provide new tools for control of disease progression and PCa treatment.

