Study type	Interventional, allocation: randomised, Intervention model: parallel assignment with 1:1 allocation ratio, Masking: double blind (subject, caregiver, investigator, outcomes assessor), Primary purpose: prevention, phase III
Date of first enrolment	July 2019
Target sample size	400
Recruitment status	Recruiting
Primary outcome(s)	Castration resistance
Key secondary outcomes	Lipid levels, Prostate cancer mortality and overall survival, Circulating cell free DNA, Fasting blood glucose, Occurrence of cardiovascular events during ADT, Quality of life

ADT, androgen deprivation therapy.

The study will be carried out in collaboration between urological departments of University Hospitals and central hospitals in Finland, the Herlev University Hospital in Denmark, the Tartu University Hospital in Estonia and Vestfold Hospital Trust in Norway (table 1).

Study data are collected and managed using REDCap electronic data capture tools hosted at Tampere University.^31 32^ Only the primary investigators, study nurses and registered study coinvestigator from each participating site will have access to the platform. All laboratory results, symptoms and results from imaging studies done at the discretion of the attending clinicians are recorded in the database. All clinical decisions besides the study drug, for example, use of early chemotherapy, abiraterone or other drugs in adjunct with ADT will be up to the discretion of the attending clinician and allowed but will also be recorded in the REDCap database.

Follow-up is continued until development of castration resistance, death or maximum of 10 years. Participants are given the opportunity to carry on with the intervention even after development of castration resistance to observe effects on survival. Unblinding will be performed after recruitment target has been reached and all participants have been followed for minimum of 12 months.

Castration resistance is defined as either PSA progression (three consecutive rises of PSA measured at least 1 week apart with two >50% increases over the nadir and PSA >2 ng/mL) or radiological progression (appearance of two or more lesions in bone scan or soft tissue enlargement as per RECIST criteria) while serum testosterone is at the castrate level (<50 ng/mL or 1.7 nmol/L).

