### Study endpoints

Primary endpoint is the time to disease progression after starting ADT/antiandrogen therapy. Secondary endpoints are (1) PCa-specific mortality and overall survival, (2) change in serum cholesterol during the intervention and its role in predicting time to disease recurrence in the placebo arm, (3) occurrence of adverse tumour traits predicting development of castration resistance in circulating cell free DNA, (4) changes in fasting blood glucose during ADT, (5) occurrence of cardiovascular events during ADT and (6) Quality of life (QoL) during ADT.

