### Study flow

Study flow and schedule is presented in figure 1 and table 2. Patients are recruited at urology outpatient clinic at urologists’ visits. If the inclusion criteria are met and the exclusion criteria are not and the participant signs informed consent form, he is given a study number (ranging between E-001 to E-400) and he receives either 80 mg atorvastatin or placebo according to the study arm randomly allocated for the study number. No blocking or other restrictions will be implemented for randomisation. Only the national study coordinator in each country will be able to see which study arm the participant has been randomised to. The participant will then receive first dose of the respective study drug randomised to his study number. The drug boxes and capsules containing atorvastatin and placebo will be identical in appearance. All researchers, nurses and study participants will remain blinded to the allocation sequence until termination of the study and closure of the study data.

**Table 2 T2:** Study flow and timing of the laboratory and blood sample collection

	Enrolment	Allocation	Follow-up‡			
Timepoint		0	6 months	12 months	18 months	24 months
Enrolment:						
Eligibility screen	x					
Informed consent	x					
Allocation		x				
Interventions:*						
Atorvastatin			x	x	x	x
Placebo			x	x	x	x
Assesments:						
Serum PSA (ng/mL)	x		x	x	x	x
Alkaline phosphatase (U/L)	x		x	x	x	x
Creatinine (µmol/L)	x		x	x	x	x
Serum creatine kinase (U/L)	x		x	x	x	x
Alanine aminotranspherase (U/L)	x		x	x	x	x
Fasting blood glucose (mmol/L)	x		x	x	x	x
Lipid levels (total cholesterol, LDL, HDL and triglycerides) (mmol/L)	x		x	x	x	x
Cell free DNA (subgroup)†	x					
QoL	x			x		x

*Allocation 1:1 to have eighter 80 mg atorvastatin or placebo daily

†Cell free DNA is measured before allocation and after occurrence of castration resistance.

‡Follow-up until disease recurrance, death or max. 10 years

HDL, high-density lipoprotein; LDL, low-density lipoprotein; PSA, prostate-specific antigen; QoL, quality of life.

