Control visits are scheduled at 6-month intervals to suit common clinical practice. Control visits are done by a clinician, complemented with measurements done by a research nurse. For each control visit the participant returns remaining capsules from the previously delivered ration and will receive a new one according to his study number. Number of the remaining capsules will be counted and saved in the REDCap, trial database, to monitor compliance. In every visit, serum PSA (ng/mL), lipid levels (total cholesterol, high-density lipoprotein (HDL), low-density lipoprotein (LDL) and triglycerides, mmol/L), alkaline phosphatase (U/L), creatinine (μmol/L), and fasting glucose (mmol/L) will be measured (table 2) and the participant is asked about symptoms that are suggestive of metastases and about possible adverse effects of the study drug. Serum creatine kinase (U/L) and alanine aminotransferase (U/L) is also measured at each visit.

Blood samples are taken and stored at 6-month intervals to monitor changes in tumour markers and occurrence of adverse tumour characteristics after initiation of ADT. QoL during the intervention will be charted once a year using validated WHOQOL-BREF QoL questionnaire.^33^

Follow-up is continued until development of castration resistance, drop out from the study, death or maximum of 10 years. Participants developing castration resistance are given an opportunity to carry on with their assigned treatment as statins have been linked to longer cancer-specific survival. Unblinding will be performed after recruitment target has been reached and all participants have been followed for minimum of 12 months.

PCa treatment apart from the study drug will be up to the discretion of the attending clinician. All laboratory results, symptoms and possible imaging results will be recorded in the REDCap database. All clinical decisions regarding early chemotherapy and imaging will be made on the discretion of the clinician and recorded in the REDCap database.

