### Statistical methods

Distribution balance of PCa clinical characteristics such as TNM stage at diagnosis, Gleason score and PSA at time of diagnosis will be presented in a patient characteristics table, stratified by study arms. Categorical variables are displayed as absolute count frequencies and relative frequencies, that is, proportion within study arm. Continuous variables are presented as median and IQR. Minimum and maximum values are not shown to ensure anonymity of the participants.

Recurrence-free survival, that is, time from ADT initiation to castration resistance, will be analysed by using Kaplan-Meier (KM) estimator, stratified by study arm. The statistical significance of the difference between the survival estimates is tested with log-rank test. No adjustments will be used for KM estimator as the study intervention is randomised. Risk of death, as well as risk for occurrence of adverse tumour traits among men receiving atorvastatin compared with men receiving placebo will be estimated using Cox proportional hazards regression.

Univariate analysis of changes in serum lipid levels is performed by calculating the difference after—before for each participant. The statistical significance of the difference between the study arms is analysed by Mann-Whitney U test (or by t-test if under normality). These results are complemented with boxplots. Multivariable analysis for difference in serum lipid levels between the study arms are performed by fitting a logistic regression model such that the study arm is used as the response variable whereas lipid level differences are used as predictors (ie, each lipid level difference as an independent predictor). Lipid levels are expected to display heavy multicollinearity; therefore, variance inflation factors (VIF) are calculated for each coefficient afterwards, and possible adjustments made by dropping predictors with extreme VIFs (>10).

The occurrence of adverse tumour genomic traits will be analysed by calculating the proportion of participants developing adverse tumour genomic traits. The statistical significance between the proportions is tested by proportions test.

The WHOQOL-BREF patient-reported outcome (PRO) of the quality-of-life is analysed by tabulating absolute and relative frequencies. χ^2^ test for homogeneity is used to test the statistical significance of the difference between the study arms of each PRO item.

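### The article ends follow-up at castration resistance yet makes mortality an endpoint, and it gives two unreconciled unblinding points, so the handling of later deaths is unsettled

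*Protocol article*

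**What the plan says.** **End of follow-up.** Study flow: "Follow-up is continued until development of castration resistance, drop out from the study, death or maximum of 10 years". Study setting (text after Table 1) gives the same rule without drop-out. The Abstract and the Table 2 footnote end follow-up at recurrence or death, the footnote adding the 10-year maximum.

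**Mortality as an outcome.** Study objective names cancer-specific and overall mortality among the secondary objectives. Study endpoints: "Secondary endpoints are (1) PCa-specific mortality and overall survival". Statistical methods assigns a Cox model to "Risk of death, as well as risk for occurrence of adverse tumour traits among men receiving atorvastatin compared with men receiving placebo", with no mention of censoring at castration resistance.

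**Text pointing past castration resistance.** Study setting: "Participants are given the opportunity to carry on with the intervention even after development of castration resistance to observe effects on survival". Study flow repeats the offer. Sample size calculation adds that a post hoc follow-up continues after the intervention, without saying whom it covers, what it collects or for how long.

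**Unblinding.** Study setting and Study flow: "Unblinding will be performed after recruitment target has been reached and all participants have been followed for minimum of 12 months". Elsewhere in Study flow: "All researchers, nurses and study participants will remain blinded to the allocation sequence until termination of the study and closure of the study data". The Abstract also has researchers, nurses and patients blinded throughout, and Table 1 lists the outcomes assessor as masked.

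**The concern.** A survival endpoint needs vital status on every randomised man up to a common end of observation. A rule that stops at castration resistance does not provide it, because cancer death in this setting normally comes after castration resistance. Under that rule the Cox model would describe death before castration resistance, not overall survival. Censoring would occur at the very event the drug is meant to delay, so observation time would differ by arm if the drug works.

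If survival were instead observed only through the optional continuation of study drug, the comparison would rest on men who chose to continue after randomisation, not on the randomised groups.

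The two unblinding points add a second uncertainty. If the code is broken at the earlier one while deaths are still accruing, cause of death may be assigned, and statins may be started in the placebo arm, with allocation known.

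**Working it through.** The article states no figure for mortality, so there is none to reproduce. The sample size of 400 belongs to the primary endpoint and does not bear on this point.

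**Inputs**
- Metastatic disease (Introduction): median 12–15 months to castration resistance, and "45 months to death in patients who have started ADT for metastatic PCa".
- Recurrent disease (Introduction): median 33 months to failure, 70 months to death.
- Longest follow-up: 10 years (120 months). Earliest unblinding: last recruit plus 12 months.
- Accrual: only described as taking several years. Assumed here: uniform over A = 36 to 60 months.

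**Step 1. Gap between the medians**
- Metastatic: 45 − 15 = 30 and 45 − 12 = 33 months.
- Recurrent: 70 − 33 = 37 months.

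**Step 2. Deaths still seen if follow-up stops at castration resistance.** Only men who die first are counted. Assume a yearly probability a of such death of 1–5%, so the monthly hazard is h = −ln(1 − a)/12. With exponential times, the share ending follow-up by death is h/(h + ln2/m), where m is the median time to castration resistance.
- Metastatic, m = 13.5 (midpoint of 12–15): 1.6% at a = 1%, 7.7% at a = 5%.
- Recurrent, m = 33: 3.8% at a = 1%, 16.9% at a = 5%.

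Most of these would be deaths from other causes.

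**Step 3. Deaths after the earliest unblinding.** With exponential survival and λ = ln2/median:
- Proportion of men dead at unblinding: P = 1 − [exp(−12λ) − exp(−λ(A + 12))]/(λA).
- Proportion dead by 10 years: D = 1 − exp(−120λ).
- Share of 10-year deaths after unblinding: 1 − P/D.

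| Group | A (months) | P | D | 1 − P/D |
|---|---|---|---|---|
| Metastatic (45) | 36 | 0.362 | 0.843 | 57% |
| Metastatic (45) | 60 | 0.458 | 0.843 | 46% |
| Recurrent (70) | 36 | 0.253 | 0.695 | 64% |
| Recurrent (70) | 60 | 0.330 | 0.695 | 52% |

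Example, metastatic, A = 36: λ = 0.01540; P = 1 − (0.8312 − 0.4774)/0.5545 = 0.362; 1 − 0.362/0.843 = 0.57.

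**Step 4. Sensitivity**
- Longer accrual (72 months, exponential): 41% metastatic (1 − 0.591) and 47.5% recurrent (1 − 0.525).
- Sequential model (exponential time to castration resistance, then exponential survival calibrated to the stated median survival; simulation): 52–67% metastatic and 65.5–78.5% recurrent for 36–60 months' accrual.

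The share therefore depends on accrual and on the survival model.

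**The case against.** A reader might infer that the plan will cut off mortality before almost all cancer deaths or else gather it open label. The article does not support that either/or.

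- **The cut-off is one side of conflicting text.** Continued study drug is offered expressly to observe survival. For a man who stops at castration resistance the intervention is over, so the post hoc follow-up can fairly be read as covering him. The Cox model is not said to censor at castration resistance, and the full protocol may hold the mechanics. This stands against calling the cut-off the settled plan. It does not remove the conflict, since four places state a stop and none refers to the later follow-up.
- **Twelve months is a minimum.** The two unblinding statements are compatible if the study terminates and the data close at or after that point. The article does not say so, and termination is not defined against the 10-year maximum.
- **Most deaths observed unblinded?** The 36–46% (metastatic) and 25–33% (recurrent) dead at earliest unblinding are shares of men. As shares of deaths the answer is about half, and its direction changes with the assumptions. Deaths before unblinding would be collected blind.
- **All-cause death is hard to misclassify.** Knowledge of the arm affects cause of death and later statin use more than whether a death is recorded.
- **Drop-out.** A reader might also set the drop-out stop in Study flow against the intention-to-treat text in Study setting. That text only offers men the chance to remain or return, so drop-out can simply mean those who decline. The conflict is minor.

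**Conclusion.** The article contradicts itself on when follow-up ends and leaves two unblinding points unreconciled. The literal stop rule would exclude nearly all cancer deaths and censor on the primary endpoint. This rests on the article's own medians and on cancer death normally following castration resistance. It does not show that investigators intend to stop there.

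On unblinding, roughly half of 10-year deaths (46–57% metastatic, 52–64% recurrent) would fall after the earliest date, given uniform accrual over 36–60 months and exponential survival. The sequential model gives higher shares and longer accrual lower ones. What is exposed is mainly prostate cancer mortality, through cause-of-death attribution, and both survival comparisons through later statin use.

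The primary endpoint and its analysis are not affected. This should be fixed, but it does not threaten the trial's main result.

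**What to change.** Reconcile the Abstract, Study setting, Study flow, the Table 2 footnote and Sample size calculation by defining two follow-up periods:

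1. **Primary-endpoint follow-up**, to castration resistance.
2. **Survival follow-up**, collecting vital status and cause of death for all randomised men, whether or not they have reached castration resistance or continue study drug, to 10 years or data closure. Mortality is analysed by allocated arm in all randomised men.

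Replace the two unblinding statements with one rule that says who is unblinded and when. Those who assign cause of death should stay blinded until the survival data close. One way is to unblind only the analysis team at the primary analysis and keep participants and sites blinded as well.

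The cost is protocol wording, one further data item per man (vital status with cause of death), and a blind and code list kept for longer.

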### Stored blood samples

Separate whole blood (for RNA and DNA isolation), plasma and serum samples are taken at each control visit at 6-month intervals and stored for mass-spectrometric and nuclear MR-based determination of serum lipidome. These samples will also be used for RNA and whole genome sequencing of mutations and genetic modifications predicting disease recurrence and metastasis, such as BRCA1/2, ERG, MYC, TP53, ATM, PTEN and AR splice variants.^34 35^ Also hypoxia markers will be measured.^36^

For participants with confirmed metastases in the bone or soft tissues, amount of cell free DNA from the plasma will be measured before ADT initiation and again at castration resistance development for sequencing and detection of genetic modifications predicting metastases.^34 35^ Selected patients are also imaged with positron emission tomography (PET) scan using 18F-2-nitroimidazolpentafluoropropylacetamide (EF5)^37^ to monitor hypoxia and fluorine-18-fluorodeoxyglucose positron emission tomography (FDG-PET) to evaluate immune responses^38^ in the primary tumour and the metastases during the atorvastatin intervention.

### Sample size calculation

In a cohort study by Harshman *et al*,^23^ among men starting ADT, 58% of the statin users and 75% of non-users of statins progress to castration resistance during median 5.8 years. We used these crude percentages for sample size calculations.

With alpha and beta values of 0.05 and 0.20 (power=0.80), sample size of 400 men will be enough to detect a risk difference with HR 0.65 (figure 2). We assume 10% drop-out rate in each study arm. The programme ‘PS—Power and sample size, V.3.1.2’ was used for the calculation.

**Figure 2 F2:**
[figure not shown]
Sample size estimation with power 0.8 as a function of HR. Calculation was made based on study by Harshman *et al.*^23^

The median time to disease progression is assumed to be 12–15 months for patients with de novo metastatic disease and 33 months for patients recurring after primary therapy.^3–7^ Therefore, the intervention will continue until castration resistance, death, or for maximum of 10 years. Post hoc follow-up will continue after the intervention. A 3 months’ difference in time to castration resistance between the study arms will be considered clinically significant.

It has to be noted that the number of studies published on this topic is low and, in the absence of randomised evidence on this topic, the power calculation is based on results of epidemiological study prone to residual bias. Therefore, an interim analysis will be performed after the first 100 participants have met the primary endpoint, that is, progressed into castration resistance. Without lifting the blinding, the power calculations are repeated to verify whether the chosen sample size has adequate statistical power to detect statistically significant difference of the effect size observed between the randomisation groups at that time. If the calculations suggest that a larger sample size is needed for the trial, the study protocol will be amended with updated recruitment target.

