## Methods and analysis

### Study setting

Study flow, study settings and other information are presented in figure 1 and table 1. The study recruitment target is 400 participants who start ADT as primary management of de novo metastatic PCa or as secondary management for PCa recurrence after localise treatment. Participants can be high-risk M0 or M1 stage, main inclusion criterion is that long-term ADT treatment is started. These men will be randomised 1:1 (200+200) to receive either 80 mg of atorvastatin daily or placebo until disease recurrence that is, development of castration resistance, death or maximum of ten years. Sample size is based on a power calculation from a previous retrospective study.^23^

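### The interim power check at 100 events is described as blinded but uses the effect observed between the arms; nobody is assigned to run it, and no cap or adjustment to the final test is stated

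*Protocol article*

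**What the plan says.** The interim is described under Sample size calculation, in the text after Figure 2. The article concedes that the planning effect comes from an epidemiological study open to residual bias. It therefore schedules a look once 100 men have reached castration resistance.

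- **Blinding:** "Without lifting the blinding, the power calculations are repeated".
- **Quantity used:** the question is whether the sample size gives "adequate statistical power to detect statistically significant difference of the effect size observed between the randomisation groups at that time".
- **Consequence:** "If the calculations suggest that a larger sample size is needed for the trial, the study protocol will be amended with updated recruitment target".

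The planning basis in the same section is "With alpha and beta values of 0.05 and 0.20 (power=0.80") and "sample size of 400 men will be enough to detect a risk difference with HR 0.65". Its event proportions are "58% of the statin users and 75% of non-users of statins progress to castration resistance during median 5.8 years", and "We assume 10% drop-out rate in each study arm".

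Study flow says that only the national study coordinators can see a man's arm, and that all researchers stay blinded until the study ends and its data are closed. Statistical methods gives a log-rank test for the primary comparison and mentions no allowance for the interim. A detailed statistical analysis plan is promised before the final analysis; it is not available here.

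**The concern.** The blinding claim and the quantity to be calculated sit in the same sentence and do not fit together. A blinded sample-size check uses pooled data only. A check based on the difference between arms is comparative, so someone must hold arm-level outcomes, and the text does not say who.

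Two things follow. First, enlarging a trial because the interim effect looks small, and then testing as if the size had been fixed, can raise the type I error of the primary test. Second, the HR at 100 events is imprecise, so the check may ask for more men even when the planning assumption is right. The article already expects enrolment to take several years, so a needless increase would be costly.

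**Working it through.** **Inputs.** Alpha 0.05, power 0.80, HR 0.65, N = 400, event proportions 58% and 75%, 10% drop-out (Sample size calculation); 1:1 allocation (Study setting); interim at 100 events. Sidedness is not stated; two-sided is assumed.

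**1. The plan's own figure.** Schoenfeld events = 4(1.96 + 0.8416)² / (ln 0.65)² = 4 × 7.849 / 0.1856 = 169.2, so 170. The mean event proportion is (58% + 75%)/2 = 66.5%. That gives N = 170/0.665 = 256, or 256/0.9 = 285 with drop-out. The stated 400 is not reproduced. It would follow from an event fraction of 170/360 = 0.472, which needs accrual and follow-up assumptions the article does not give. This is a separate matter, and it errs towards a larger trial.

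**2. Planned events at N = 400.** With drop-out, 400 × 0.9 × 0.665 = 239. Without, 400 × 0.665 = 266. Power at HR 0.65 is 0.91 and 0.94.

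**3. Precision of the interim HR.** SE(ln HR) = 2/√100 = 0.20. If the true HR is 0.65, the observed HR has a 95% range of 0.44 to 0.96. Putting the observed HR into the formula in step 1 gives:

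| Percentile of observed HR | Observed HR | Events required |
|---|---|---|
| 10th | 0.503 | 67 |
| 25th | 0.568 | 99 |
| 50th | 0.650 | 170 |
| 75th | 0.744 | 359 |
| 90th | 0.840 | about 1,030 |

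**4. Chance that the check asks for more men although HR is 0.65.** The weakest HR that d events detect with 80% power is exp(−2 × 2.8016/√d).

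- d = 239: HR 0.696; (ln 0.696 − ln 0.65)/0.20 = 0.34; probability 37%.
- d = 266: HR 0.709; (ln 0.709 − ln 0.65)/0.20 = 0.44; probability 33%.

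**5. Type I error with an ordinary final test.** Under no effect, let Z1 be the statistic at 100 events and Z2 the independent statistic from later events. The final events d are set from the observed HR and never fall below plan. The final statistic is (10·Z1 + √(d − 100)·Z2)/√d, with rejection beyond ±1.96. The article states no cap, so caps are assumed. With 239 planned events:

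| Cap (× plan) | Raised up to the cap | Raised only if the requirement is within the cap |
|---|---|---|
| 1.25 | 5.3% | 5.0% |
| 1.5 | 5.6% | 4.9% |
| 2 | 5.9% | 4.9% |
| 5 | 6.5% | 5.0% |
| 10 | 6.8% | 5.3% |

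As a sensitivity check, a plan of 170 events under the first rule gives 6.1% at 2× and 7.2% at 10×. Under the second rule, plans of 170 to 266 events give 4.7% to 5.1% for caps from 1.5× to 5×, and about 5.7% to 5.8% at 20×.

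**The case against.** **The check can be masked.** The required events depend only on the absolute size of ln HR, so the sum can be done on groups labelled A and B. The national coordinators hold allocations and could supply the labels. This stands against any reading that the check must unblind the trial. It does not rescue the text: an A/B calculation is still comparative, and no one is given the task or the data.

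**A raised target gives little away.** A reader might infer that it would destroy the blind. Under a symmetric rule it would show at most the size of the interim effect, not its direction or any man's allocation. Working back to that size also needs a known rule, and none is stated. This stands.

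**The analysis plan may supply a cap or an adjustment.** It may, so the fair wording is that none is stated in this document. But the plan is promised only before the final analysis, and nothing ties it to the 100-event look. The rule has to be fixed before that look.

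**The type I error depends on an assumed rule.** A reader might infer that it necessarily exceeds 5%. The documents do not support that: a restricted rule keeps it near 5%, and the largest figures need caps of 5 to 10 times, which scales to 2,000 to 4,000 men. Nor is any efficacy test planned at the interim.

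**Noise does not dominate.** Because the target can only rise, requirements below plan change nothing. At HR 0.65 the target is left alone 63% to 67% of the time. This stands, so it would be too strong to say that the new size is driven mainly by noise.

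**A pooled check misses the purpose.** The article doubts its planning effect, and a check at fixed HR 0.65 does not address that doubt. It would also pass almost automatically under the article's own event proportions (239 to 266 expected against about 170 needed). This is a fair cost of that option, and the reason to offer a second one.

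**Conclusion.** The concern holds in this form. The interim step contradicts itself: it claims an intact blind for a calculation that needs arm-level data, in a trial whose researchers all stay blinded and where no one is assigned to do it. The rule only increases the target, depends on the observed effect, and is followed by an ordinary log-rank test with no cap or adjustment stated here.

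The effect on type I error is modest and conditional. With 239 planned events it is 5.3% to 6.8% if the target is raised up to a cap of 1.25 to 10 times, and about 5% if it is raised only for requirements within a cap of up to 5 times. The chance of a call for more men when HR 0.65 is true is 33% (266 planned events) to 37% (239).

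These figures assume two-sided testing, the article's crude event proportions, the usual normal approximation for the log-rank statistic, and caps that the article does not give. If the analysis is reached with fewer events than 239, both figures rise: with 170 planned events the chance of a call for more men is about 50%.

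**What to change.** Rewrite the interim paragraph in one of two ways, before the 100th event.

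1. **A truly blinded check.** Keep the design HR at 0.65. Use only pooled events, accrual and drop-out to judge whether the required events (about 170 by the Schoenfeld formula) will be reached, and extend recruitment or follow-up on that basis alone. Cost: one paragraph, no alpha and no extra staff. Downside: the trial cannot react to an effect smaller than planned.

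2. **An effect-based re-estimation**, if reacting to the observed effect is the purpose, as the article's reasoning suggests. Have a statistician outside the trial team run it. Fix beforehand a capped rule and a pre-weighted final statistic (Cui-Hung-Wang type). Replace the claim of an intact blind with a statement of who sees arm-level data. Cost: an outside statistician, and a primary test that gives men added later less than their natural weight if the target is raised.

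Under either option, the sample-size section, the blinding statement in Study flow and the primary test in Statistical methods should be made to agree.
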